### 4.4. Criteria for Discontinuation of Trial Treatment

The criteria for the discontinuation of a trial are as follows:

(1) The participant refuses further participation or withdraws consent; (2) termination of the entire study; (3) occurrence of a spontaneous pregnancy; (4) failure to adhere to the study rules; (5) attendance of fewer than 75% of the exercise sessions by the participant in the intervention group; (6) occurrence of any other intervention or surgery during the study period that may alter the study outcome; (7) undesirable events related to the treatment, such as acute pain, musculoskeletal complaints, or acute mental or physical trauma preventing continuation of the study; (8) presence of a newly diagnosed malignancy; (9) any situation where oral therapy or physiotherapy is deemed unfit to continue according to the decision of the physician and physiotherapist.

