#### 2.3.1. Primary Outcome

The primary outcome is the change in FSH and AMH levels compared with the levels before. Spontaneous pregnancy during the study period will be recorded as a primary outcome measure.

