### 2.6. Recruitment

Patients meeting the eligibility criteria will be recruited from the Assisted Reproduction Center of Semmelweis University, Hungary. Detailed information about the study will be provided verbally and in writing by the examining physician. Research subjects are informed that in this clinical trial we intend to compare three groups of infertile women. The group receiving only per os complementary therapy, the group receiving per os complementary therapy and walking, and the group receiving per os complementary therapy and a specific exercise program will be tested. We will also inform prospective participants that participation in the research is voluntary and that the anonymized data obtained will be summarized and subjected to statistical analysis. Participation in the study will take approximately 12 weeks.

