### 4.7. Efficacy Assessments

The efficacy of the trial treatment will be evaluated using a comprehensive set of parameters measured at the 3-month follow-up. Participants’ weight, height, and BMI will be recorded. This will help in assessing any changes in body composition resulting from the intervention. The regularity and characteristics of participants’ menstrual cycles will be monitored from the start to the end of the study. This continuous observation aims to identify any improvements or alterations in menstrual health. Hormonal evaluations, including levels of AMH, FSH, LH, E2, PRL, TSH, and 25-OH-D3 vitamin, will be conducted at the conclusion of the study as well. As a primary outcome, the change in FSH and AMH levels will be administered. The measurement of progesterone will help evaluate the sufficiency of the luteal phase, which is critical for reproductive health. These measures will provide insights into the hormonal balance and ovarian function of the participants. The FSFI questionnaire will be administered to assess changes in sexual function. This self-reported measure will provide valuable data on the impact of the intervention on participants’ sexual health. The occurrence of spontaneous pregnancy during the study period will be recorded as a primary outcome measure. This will directly indicate the effectiveness of the intervention in improving fertility. These comprehensive assessments will collectively provide a thorough evaluation of the intervention’s efficacy.

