## Figures and Tables

**Figure 1 life-15-00018-f001:**
[figure not shown]
Trial design.

**Table 1 life-15-00018-t001:** Study Assessments and Procedures.

	Screening	Baseline (2–4. Day of Menstrual Cycle)	Baseline (21–22. Day of the Same Cycle)	3 Months (2–4. Day of Cycle)	3 Months (21–22. Day of the Same Cycle)
Assessment					
Investigator meetings	✓				
Informed consent	✓				
Demographics, medical, and family history	✓				
Body composition assessment (Weigh, Height, BMI)	✓			✓	
Menstrual cycle	✓			✓	
Hormone levels (AMH, FSH, LH, E2, PRL, TSH, 25-OH-D3 vitamin)		✓		✓	
Progesteron		✓	✓		✓
FSFI questionnaire		✓		✓	
Spontaneous pregnancy				✓	

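### Women who conceive reach one primary outcome but cannot give the 3-month FSH/AMH sample for the other, and conceptions in the final cycle have no scheduled check

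*Protocol article*

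**What the plan says.** Section 2.3.1 of the protocol article sets two kinds of primary outcome. For the hormones: "The primary outcome is the change in FSH and AMH levels compared with the levels before". For pregnancy: "Spontaneous pregnancy during the study period will be recorded as a primary outcome measure". Section 4.7 repeats the second: "The occurrence of spontaneous pregnancy during the study period will be recorded as a primary outcome measure".

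Section 4.4 lists "occurrence of a spontaneous pregnancy" as criterion 3. Its heading is "Criteria for Discontinuation of Trial Treatment", but its opening line reads "The criteria for the discontinuation of a trial are as follows". Neither says whether outcome follow-up continues afterwards.

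Table 1 ticks spontaneous pregnancy in one column only, headed "3 Months (2–4. Day of Cycle". The second FSH/AMH sample is in the same column. One later column follows, on days 21–22 of that cycle, where only progesterone is ticked.

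Section 2.5 compares baseline with three-month laboratory values within groups by paired tests, and compares the three groups by ANOVA or Kruskal–Wallis. Pregnancy is reported as a percentage and compared by chi-square or Fisher's exact test. On duration, section 2.6 states: "Participation in the study will take approximately 12 weeks".

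**The concern.** The day 2–4 sample presupposes a menstrual period. A woman who is pregnant at 3 months has none, so she has no FSH/AMH value as the plan defines it, and reaching one primary outcome removes her from the other.

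This loss is unlikely to be random. The Introduction expects AMH to rise, FSH to fall and spontaneous pregnancies to occur together, and section 4.7 treats pregnancy as a direct sign that the intervention works. On the trial's own hypothesis, the women lost from the hormone comparison tend to be good responders, and more are lost from the arm that works best. The groups being compared are then selected after randomisation by outcome.

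A second, smaller matter is the window for the pregnancy outcome. Table 1 has no check for a conception in the last cycle, and the articles's sections do not agree on when the study period ends.

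**Working it through.** **1. The plan's own sample size.** Inputs from section 2.4: one-way ANOVA, three groups, f = 0.4, alpha 0.05, power 0.95. With noncentrality N·f² and degrees of freedom (2, N − 3), power is 0.9488 at N = 99 and 0.9547 at N = 102. So 102 is the smallest balanced total, as stated. The dropout inflation is 34 / (1 − 0.15) = 40 per group, or 120 in total, also as stated. The 15% allowance brings 40 down to exactly 34, so it covers pregnancies only if they are counted within the 15%.

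**2. Loss of numbers.** Suppose a fraction p conceives and is lost on top of the 15%. Evaluable N = 120 × 0.85 × (1 − p). No conception rate is given, so p is an assumption.

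| p | Evaluable N | Power |
|---|---|---|
| 5% | 96.9 | 0.944 |
| 10% | 91.8 | 0.932 |
| 15% | 86.7 | 0.916 |
| 20% | 81.6 | 0.898 |

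The loss of power is modest.

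**3. Selective loss.** Let hormone response be standard normal within an arm, scored so that higher is better. Let the fraction p with the highest latent score conceive, where that score correlates r with response. The mean among women who do not conceive then shifts by −r·g(p), with g(p) = φ(z) / (1 − p) and z the (1 − p) normal quantile:

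- g(0.05) = 0.1086
- g(0.10) = 0.1950
- g(0.15) = 0.2743
- g(0.20) = 0.3500

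For an assumed true difference of 0.5 SD, the observed difference is 0.5 − r × [g(p in exercise arm) − g(p in comparator)].

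| Conceiving, exercise vs comparator | r = 0.3 | r = 0.5 |
|---|---|---|
| 10% vs 5% | 0.474 | 0.457 |
| 15% vs 5% | 0.450 | 0.417 |
| 20% vs 5% | 0.428 | 0.379 |

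For example, 20% vs 5% with r = 0.5 gives 0.5 − 0.5 × (0.3500 − 0.1086) = 0.379. A simulation with one million draws per arm agrees to within 0.005. If the arms conceive equally often, the two shifts cancel and the contrast is unbiased.

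**4. The final cycle.** A conception before the 3-month visit shows itself when no period comes. A conception in the cycle that begins with that visit does not. The last contact is day 21–22, before the next period is due in a 28-day cycle, and its column has no pregnancy tick.

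**5. The end of the study period.** Take 28-day cycles and count from the baseline visit. The 3-month visit falls at 84 days and the day 21–22 visit about 18.5 days later: 102.5 / 7 = 14.6 weeks, against about 12 in section 2.6. For other cycle lengths the answer depends on an unstated visit rule. With 35-day cycles, the first eligible visit at or after day 84 gives (105 + 18.5) / 7 = 17.6 weeks, while the visit nearest day 84 gives (70 + 18.5) / 7 = 12.6 weeks.

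**The case against.** A reader might infer that conceptions are generally missed. The article does not support that. Sections 2.3.1 and 4.7 record pregnancy over the whole study period, section 4.7 has menstrual cycles monitored from start to end, and criterion 3 can be applied only to a pregnancy already noticed. A Table 1 tick is not the sole moment of observation either: menstrual cycle is ticked only at screening and 3 months, yet it is monitored throughout. Only the final cycle lacks a scheduled check.

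A reader might also infer that conceiving ends a woman's participation. That is one reading of section 4.4, whose heading confines it to treatment. Stopping treatment at a primary event is not in itself a contradiction. But even on the treatment-only reading, the day 2–4 hormone value does not exist.

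Stronger figures are tempting. With 10–20% conceiving and r of 0.3–0.7, the exercise arm's mean is understated by 0.06–0.25 SD (0.3 × 0.1950 to 0.7 × 0.3500). That is a one-arm bias; the other arms lose women too, and the contrast moves less. Saying that a quarter of exposure goes unobserved means taking the longer study period and counting the baseline cycle in full, and the article settles neither.

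Finally, denominators and missing-data handling are commonly left to an SAP or full protocol, neither of which is shown. That is fair for the detail of the analysis. It does not remove the conflict among the stated outcomes, the discontinuation rule and the visit schedule, all of which are in the article.

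**Conclusion.** The concern holds in a bounded form. As scheduled, a woman pregnant at 3 months cannot give the second FSH/AMH sample, so the hormone comparison applies only to women not pregnant then and is biased against an arm with more conceptions. The direction follows if conception goes with better hormone response, which is the article's own expectation. The size is not known: with an assumed true difference of 0.5 SD, assumed conception rates of 10–20% against 5%, and assumed correlations of 0.3–0.5, the observed difference is about 0.38–0.47 SD. The sample size calculation itself is correct.

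Pregnancy ascertainment has a narrower gap: the final cycle has no scheduled check, and the end of the study period is inconsistent between section 2.6 and Table 1. The documents do not support a claim that pregnancies are missed throughout, or that women who conceive are certainly withdrawn from follow-up.

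**What to change.** Reconcile sections 2.3.1, 2.6, 4.4 and 4.7 with Table 1. None of the following changes or judges any treatment-stopping rule.

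- **Follow-up.** State that women who conceive remain in outcome follow-up and count as events, with all randomised women as the denominator.
- **Window.** Define one pregnancy window from randomisation, the same for all arms and long enough to cover the last visit whatever the cycle length. Add a telephone or records check about 4 weeks after the last visit, and amend the Table 1 row to match.
- **Hormone analysis.** State that the main FSH/AMH comparison applies to women not pregnant at 3 months, and report the number excluded for pregnancy in each arm. Add a sensitivity analysis that keeps women who conceive, for example by ranking conception as the best outcome. Making such a composite the main analysis is a debatable choice, because it merges outcomes that section 2.3.1 lists separately, and is not required here.

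The cost is one short contact per participant, one corrected table row and one added analysis.

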### 4.5. Discontinuation of the Study

The study will be terminated early if the Institutional Review Board (IRB) identifies any of the following: serious adverse drug effects; a newly diagnosed malignancy; or participants encountering unexpected, significant, or unacceptable risks (such as death).

### 4.6. Baseline Assessments

Baseline assessments will adhere to the trial’s standard operating procedure (SOP). During the first visit, between days 2 and 4 of the cycle, a laboratory examination will be conducted, including hormone levels of AMH, FSH, LH, E2, PRL, TSH, 25-OH-D3 vitamin, and progesterone. Baseline progesterone will be measured between days 21 and 22 of the same cycle. The FSFI questionnaire will also commence during this phase.

### 4.7. Efficacy Assessments

The efficacy of the trial treatment will be evaluated using a comprehensive set of parameters measured at the 3-month follow-up. Participants’ weight, height, and BMI will be recorded. This will help in assessing any changes in body composition resulting from the intervention. The regularity and characteristics of participants’ menstrual cycles will be monitored from the start to the end of the study. This continuous observation aims to identify any improvements or alterations in menstrual health. Hormonal evaluations, including levels of AMH, FSH, LH, E2, PRL, TSH, and 25-OH-D3 vitamin, will be conducted at the conclusion of the study as well. As a primary outcome, the change in FSH and AMH levels will be administered. The measurement of progesterone will help evaluate the sufficiency of the luteal phase, which is critical for reproductive health. These measures will provide insights into the hormonal balance and ovarian function of the participants. The FSFI questionnaire will be administered to assess changes in sexual function. This self-reported measure will provide valuable data on the impact of the intervention on participants’ sexual health. The occurrence of spontaneous pregnancy during the study period will be recorded as a primary outcome measure. This will directly indicate the effectiveness of the intervention in improving fertility. These comprehensive assessments will collectively provide a thorough evaluation of the intervention’s efficacy.

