Despite these promising findings, further research is needed to confirm these effects due to the limited number and sample size of previous studies and the current ambiguity in exercise recommendations for improving fertility outcomes.

In this study, we present a novel and innovative therapeutic exercise protocol specifically designed for pelvic region rehabilitation and ovarian rejuvenation. The therapeutic exercises focus on improving fertility, rehabilitation of the pelvic region (including re-education of the pelvic floor muscles), teaching correct posture, improving the pelvic-lumbar core stabilization system, restoring optimal muscular function of the diaphragm, and activating the parasympathetic nervous system through learning stress-relieving breathing and relaxation. These exercises are expected to enhance pelvic circulation and improve muscle function, which are crucial for reproductive health, especially in patients with diminished ovarian reserve (DOR).

The primary objective of this study is to assess the ovarian rejuvenating effect of this specific exercise program before IVF/ICSI cycles or spontaneous pregnancy, confirming the reproductive efficacy of this regimen. We also aim to improve stimulation and oocyte quality in patients who meet the inclusion criteria, partly by improving pelvic and ovarian circulation (ovarian rejuvenation exercise, the subject of this study) and partly by enhancing cumulus corona radiata and granulosa cell function (per os rejuvenation therapy).

It is expected that our results will show that AMH will be increased, basal FSH levels will be decreased, cycle length will be optimized (getting closer to 28–30 days), fertility rates and stimulation will be improved, and spontaneous pregnancy will be detected at the end of the process. If this investigation confirms the efficacy of the specific exercise program in DOR patients, this could make a useful contribution to fertility treatment in this poorly manageable patient population.

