### 2.2. Eligibility Criteria

#### 2.2.1. Inclusion Criteria

Participants who meet the following inclusion criteria will be included: (1) female of reproductive age 20–42 years; (2) BMI: 18.5–30 kg/m^2^; (3) regular menstruation; (4) anti-Müllerian hormone (AMH) <  1.1 ng/mL; (5) hormone levels: TSH < 2.5 mIU/mL, vitamin D3: >75 nmol/L, Prolactin: <24 ng/mL; (6) understanding the study design, risks, and benefits, and providing informed consent; and (7) the ability to comply with the study protocol.

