#### 2.3.2. Secondary Outcomes

The secondary outcomes include: optimization of E2 and LH levels; optimization of menstrual cycle length; change in BMI level; improvement in quality of life using the FSFI questionnaire; and comparing the effectiveness between the 3 study groups.

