### 2.4. Sample Size

A parallel, 3-group design will be used. We determined the sample size using G*Power 3.1.9.7 software. We employed one-way analysis of variance (ANOVA) due to consideration of three different therapies. The effect size was estimated at 0.4. We set alpha to 0.05 and power to 0.95. Consequently, the software provided an estimated total sample size of 102, resulting in 34 cases per group. To account for a potential dropout rate of 15%, we increased the sample size to 40 participants per group. Therefore, the total sample size needed for the study is 120 participants [31].

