### 2.5. Statistical Methods

Descriptively, we intend to calculate the mean, standard deviation, minimum, maximum, and range of data, while the occurrence of spontaneous pregnancy will be presented as a percentage. For the evaluation of results, after conducting the Shapiro–Wilk normality test, paired T-tests or Wilcoxon tests will be used to compare baseline and three-month laboratory results within each group, and one-way analysis of variance (ANOVA) or Kruskal–Wallis’s test, along with Tukey’s post hoc test, will be used for comparison among the three groups. Chi-square tests or Fisher’s exact tests are planned to be applied for comparing the numbers or percentages between groups.

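### Luteal progesterone is drawn on fixed cycle days 21–22 although cycle length is expected to change, so a cycle-length shift can look like a change in luteal function

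*Protocol article*

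**What the plan says.** All places are in the protocol article.

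- **Baseline draw.** Section 4.6: "Baseline progesterone will be measured between days 21 and 22 of the same cycle".
- **Follow-up draw.** In Table 1, the only progesterone tick after baseline is in the column headed "3 Months (21–22. Day of the Same Cycle)".
- **Interpretation.** Section 4.7 counts progesterone among the efficacy parameters: "The measurement of progesterone will help evaluate the sufficiency of the luteal phase".
- **Expected change in cycles.** Section 1 predicts that "cycle length will be optimized (getting closer to 28–30 days)". Section 2.3.2 lists "optimization of menstrual cycle length" as a secondary outcome.
- **Entry.** The third criterion in Section 2.2.1 is "3) regular menstruation". Section 2.1 asks in addition that menstruation be normal. Neither gives a length in days.
- **Analysis.** Section 2.5: "paired T-tests or Wilcoxon tests will be used to compare baseline and three-month laboratory results within each group". The three groups are then compared by ANOVA or Kruskal–Wallis.

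**The concern.** A day-21 sample has a fixed meaning only if ovulation falls on about the same cycle day each time. The protocol expects its own treatment to move cycle length, and that can move ovulation relative to day 21. A paired comparison of two day 21–22 values may then mix a change in corpus luteum function with a change in where on the progesterone curve the blood was taken.

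Randomization does not remove this. Cycle length during follow-up is a post-randomization variable that treatment is expected to affect. If one arm's cycles change more than another's, its sampling position changes more as well.

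At stake is the reading of progesterone as luteal sufficiency. The trial could report better or worse luteal function when only the timing moved.

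**Working it through.** **The plan's own figure.** The document gives no figure for sampling position. Its one calculation is the sample size ("The effect size was estimated at 0.4", alpha 0.05, power 0.95, three groups). A noncentral F calculation gives power 0.9488 at N = 99 and 0.9547 at N = 102, so 102 is reproduced. Then 34 / 0.85 = 40 per group, or 120 in total. Progesterone does not enter this, so the point leaves it untouched.

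**Step 1: position relative to the next menses.** Input from the document: sampling days 21 and 22. The cycle lengths are chosen for illustration.

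Days before next menses = cycle length + 1 − sampling day.

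| Cycle length | Day 21 | Day 22 |
|---|---|---|
| 24 | 4 | 3 |
| 28 | 8 | 7 |
| 32 | 12 | 11 |
| 34 | 14 | 13 |

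A woman who goes from 24 to 28 days is sampled 4 days further from her next menses.

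**Step 2: position relative to ovulation.** Assumption, not in the document: luteal length 14 days (range 12–16), unchanged by treatment.

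Ovulation day = cycle length − luteal length. Days after ovulation = sampling day − ovulation day.

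| Luteal length | 24-day cycle | 28-day cycle | Shift |
|---|---|---|---|
| 12 | 9–10 | 5–6 | 4 days |
| 14 | 11–12 | 7–8 | 4 days |
| 16 | 13–14 | 9–10 | 4 days |

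For a long cycle with a 14-day luteal phase, going from 32 to 29 days moves the draw from 3–4 to 6–7 days after ovulation. Each day of change in follicular length moves the draw by one day.

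**Step 3: the case where there is no artefact.** Suppose the same 24-to-28-day change is entirely luteal, from 14 to 18 days. Ovulation is on day 24 − 14 = 10 before and 28 − 18 = 10 after. The draw stays 11–12 days after ovulation, and a changed value would reflect a real luteal change. The concern therefore depends on a mainly follicular shift.

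**Step 4: possible size, illustration only.** Assume a bell-shaped progesterone curve that peaks 7 days after ovulation, with SD 2.5 to 4 days, and unchanged luteal function. Ratio of the later to the earlier measured value, averaged over days 21 and 22, with a 14-day luteal phase:

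| Cycle change | SD 2.5 | SD 3 | SD 4 |
|---|---|---|---|
| 24 to 28 | 4.65 | 2.95 | 1.85 |
| 26 to 28 | 1.59 | 1.38 | 1.20 |
| 32 to 29 | 2.51 | 1.91 | 1.45 |
| 26 to 30 | 1.36 | 1.24 | 1.13 |

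The result is sensitive to luteal length. With a 12-day luteal phase, 24 to 28 days moves the draw from 9–10 to 5–6 days after ovulation. Those are the positions in the last row, so the ratio is only 1.13 to 1.36. The day shifts in Steps 1 and 2 are arithmetic; these ratios depend on an assumed curve.

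**The case against.** A reader might infer that any cycle-length change will appear as altered luteal function, and that the arms will be biased differently. The document supports neither as a certainty.

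- **Phase of the shift.** The document does not say which part of the cycle is expected to change. If the luteal phase itself lengthens, the reading is not an artefact. This stands, so the right word is can.
- **Range of cycles.** Menstruation must be normal as well as regular, which narrows the population, and no distribution or expected shift in days is given. The 24-, 32- and 34-day examples are therefore illustrations. Still, a predicted move towards 28–30 days implies that some women start outside that range.
- **Arms.** The expected change in cycle length is not stated by arm, and all three arms take the supplements. A differential artefact is plausible but not shown.
- **Weight.** Progesterone is not among the outcomes in Sections 2.3.1 and 2.3.2. A reader who took this as a threat to the main results would be wrong.
- **What is not shown.** Cycles are monitored throughout (Section 4.7), Section 4.6 refers to an SOP, and a timing adjustment could sit in an analysis plan. The absence of an adjustment is therefore not a finding. The fixed sampling days and their interpretation, however, are both in the article.

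**Conclusion.** The point holds as a minor one. Followed as written, the schedule can confound a change in progesterone with a change in sampling position. The shift is one day per day of follicular change, for example 4 days when a cycle goes from 24 to 28 days. How far this moves measured progesterone is unknown. It depends on the baseline cycle lengths, the phase that changes and the shape of the curve, none of which the document gives. The artefact may differ by arm.

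The conclusion assumes that a material part of any cycle-length change is follicular and that some women enter with cycles away from 28–30 days. It reaches only the luteal-sufficiency reading in Section 4.7. The FSH, AMH and pregnancy results and the sample size of 120 are unaffected.

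**What to change.** At both time points, schedule the progesterone sample from each woman's own recorded recent cycle length instead of fixed days 21–22, for example about 7 days before the expected next menses. That is day = cycle length + 1 − 7: day 18 for a 24-day cycle, day 22 for 28 and day 26 for 32. With a 14-day luteal phase, each is 8 days after ovulation. Cycle length is already collected at screening and monitored to the end of the study.

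Where the date of the next menses is available, record it and use it only for a sensitivity analysis of timing. Do not restrict the main between-arm comparison to samples inside an observed timing window. That selects women on a post-randomization variable which treatment may change, and can itself bias the comparison. Adjusting the main comparison for observed timing carries the same risk.

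**Cost.** Draws must be scheduled individually. Some timing error remains when a cycle departs from its recent length, and the rule still relies on a fairly stable luteal phase. The sensitivity analysis needs one date that falls after the last scheduled visit and does not exist for women who conceive in the sampled cycle. The sample size and treatment do not change.
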